**Objective:**

This prospective cohort study seeks to characterize the PPGR variability among individuals with diabetes living in India and to identify factors associated with these differences.

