### Follow-Up Procedures

Participants are followed for 14 days. They are instructed to wear the CGM and heart rate monitor. The heart rate monitor is to be always worn, including during sleep, and only removed for recharging. Participants are also asked to check their capillary glucose on days 2 through 6 before breakfast and dinner.

Participants log their full dietary intake using the study app or logbook over the 14-day study period, including all standardized test meals and free-living foods (including snacks), beverages (including water), and medications. Participants also log all exercise.

Participants are required to consume protocol-specified meals and to perform light activity, as described in Table 1. The standardized meals consist of vegetarian breakfast foods which participants are to prepare in their homes.

The meals vary in their proportion of carbohydrate, fiber, protein, and fat (refer to Table 2).

**Table 1 table1:** Meal schedule during the at-home study period.

Day and timing			Meal type
**1**			
	Breakfast	Fasting	
	Lunch	As desired	
	Dinner	As desired	
**2**			
	Breakfast	Perceived healthy meal	
	Lunch	Post meal exercise	
	Dinner	Typical mixed protein with dinner	
**3**			
	Breakfast	Fiber supplement with standardized test meal	
	Lunch	Premeal exercise	
	Dinner	Alternative mixed protein with dinner	
**4**			
	Breakfast	Fiber supplement before standardized test meal	
	Lunch	As desired	
	Dinner	As desired	
**5**			
	Breakfast	Protein supplement with standardized test meal	
	Lunch	As desired	
	Dinner	Alternative mixed protein with dinner	
**6**			
	Breakfast	Protein supplement before standardized test meal	
	Lunch	Added fiber with lunch	
	Dinner	Alternative mixed protein with added protein	
**7**			
	Breakfast	Regular breakfast	
	Lunch	Added fruit	
	Dinner	Cooled carbohydrate	
**8**			
	Breakfast	Regular breakfast with added protein	
	Lunch	Added fruit with protein	
	Dinner	Regular carbohydrate	
**9**			
	Breakfast	Protein followed by carbohydrate	
	Lunch	Water 30 minutes before lunch	
	Dinner	As desired	
**10**			
	Breakfast	Standardized test meal	
	Lunch	As desired including dessert	
	Dinner	Protein followed by carbohydrates and vegetables	
**11**			
	Breakfast	Standardized test meal with postmeal exercise	
	Lunch	As desired including desert and cinnamon	
	Dinner	Vegetables followed by protein then carbohydrates	
**12**			
	Breakfast	Standardized test meal with postmeal exercise	
	Lunch	As desired	

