	Dinner	As desired finishing eating by 8 PM	
**13**			
	Breakfast	Water before late breakfast + postmeal exercise	
	Lunch	Low glycemic index lunch	
	Dinner	Low glycemic index dinner + finish dinner by 8 PM + exercise after meal	
**14**			
	Breakfast	Water before late breakfast + exercise after meal	
	Lunch	Low glycemic index lunch + exercise after meal	
	Dinner	Low glycemic index dinner + finish dinner by 8 PM + exercise after meal	

**Table 2 table2:** Nutritional composition of standardized test meals.

Meal characteristics	Meal type		
	Carbohydrate	Added fiber	Added protein
Example meal	2 aloo parathas with curd	2 aloo parathas with curd + fiber supplement	2 aloo parathas with curd + protein supplement
Energy (kcal)	474.4	506.4	594.4
Carbohydrate (g)	61.5	64.1	62.9
Fat (g)	12.5	12.5	14.6
Protein (g)	7.7	7.8	31.9
Fiber (g)	8.3	21.9	8.3
Carbohydrate (% energy)	51.9	50.6	42.3
Fat (% energy)	23.8	22.3	22.1
Protein (% energy)	6.46	6.05	21.4

Participants are instructed to fast for a minimum of 8 hours before and 3 hours after consuming the standardized breakfast meal; during these fasting periods, limit exercise and drink only still (not sparkling) water, tea, or coffee in moderation; and eat the meal, in its entirety, within 20 minutes. After completing the postmeal fasting period on standardized test meal days, participants may consume other foods as they normally would unless there are other meal modifications specified by the protocol later the same day.

On other days, participants are asked to consume normal foods with protocol-specified constraints. For example, on different days, participants vary the types of mixed protein (eg, different types of lentils with or without added protein), ordering with the type of foods consumed (eg, protein before carbohydrate vs protein with carbohydrate), consume water before their meal, go for a walk after eating, or eat what they perceive to be a healthy meal. Where applicable, participants are given several options as to which of their usual foods are acceptable for each protocol specified food modification.

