During the follow-up period, participants are contacted by phone and text messages to ensure protocol compliance. For participants using the study-specific smartphone apps, a web dashboard is used to monitor the completeness of dietary logging and CGM scanning, with outreach to participants initiated when missing data is detected. Participants using paper logs and a CGM reader, and therefore for whom no dashboard information is available, are contacted daily to ask about protocol compliance. Ad hoc midstudy visits are used to further ensure accurate data collection. If the outreach identifies a problem with a CGM (ie, it was damaged, fell off, or malfunctioned), study staff provide a replacement within 24 hours during which time participants are asked to pause their meal protocol and restart once their CGM has been reapplied and recalibrated. If a test meal was not consumed as intended, participants are provided with the option to repeat the meal.

On day 15, participants are asked to remove their CGM. If need be, study staff help record or correct missing or inaccurate food, activity, and medication data.

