### Statistical Analysis Plan

The study’s primary outcome is PPGR. Following the Wolever and Jenkins method [31], as adapted by Zeevi et al [18], Mendes-Soares et al [20], and Berry et al [32], logged meal times and continuous glucose measurements will be used to calculate the incremental area under the curve. Before conducting analyses, meals logged less than 30 minutes apart will be merged and meals logged within 90 minutes of other meals will be removed. Meals that are very small (<15 g and <70 calories), very large (>1 kg), with implausibly low PPGR values (ie, a PPGR < 5 mg/dL·h after consuming ≥ 40 g of carbohydrates), that are incompletely logged, and which are consumed in the first and last 12 hours of the CGM connection will also be removed. To reduce noise, the median of all glucose values from the 30-minute period before the meal will be taken as the initial glucose level, above which the incremental area will be calculated. Meals that had incomplete glucose measurements in the time window of 30 minutes before and 2 hours after the logged mealtime will be filtered out.

Descriptive statistics will be used to plot the range of PPGRs responses to standardized test meals as well as the correlation between PPGR and the nutritional composition of the logged meals (ie, carbohydrates, fat, and protein).

A machine learning predictor will be developed based on stochastic gradient boosting regression (XGBoost, version 2.2.1; The XG Boost Contributors) [33] using the XGBRegressor class. PPGR will be predicted as the sum of predictions from thousands of decision trees. Trees will be inferred sequentially, with each trained on the residual of all previous trees. The features incorporated in each tree are selected by an inference procedure from features representing meal content (ie, calorie, protein, carbohydrate, and fiber content), meal timing, baseline demographics (ie, age, sex, predominant diet, health conditions, family history, and current medications), baseline survey results (ie, WHO STEPS, WHO-5, Diabetes Distress School, Wilson Adherence Scale, and Pittsburgh Sleep Quality), baseline biometric values (ie, blood pressure, heart rate, weight, height, and body measurements at the upper arm, thigh, calf, waist, and hips), baseline laboratory values (complete blood count, HbA_1c_, blood electrolytes, creatinine, cholesterol, and urinalysis), as well as CGM, heart rate, and activity data.

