## Discussion

### Study Implications

This study will provide the first large scale examination of variability in blood glucose responses to food in India and will be among the first to estimate PPGR variability for individuals with T2D in any jurisdiction. We hypothesize that there will be substantial interindividual variability in PPGR and that, based on the data collected from this study, machine learning models will be able to accurately predict individual PPGR responses. This will facilitate the prescription of truly personalized diets for individuals with T2D.

These results will be particularly important in the context of the rapidly rising prevalence of T2D in India [34]. Along with medications and physical activity, diet is a key tenant of effective blood glucose control [15]. Like in other jurisdictions, guidelines call for individualization of meal planning, which is sometimes referred to as “Medical Nutritional Therapy.” Despite this, personalization of dietary plans are generally based upon broad constructs like age, activity level, health status, and preferences, and, for all patients, tend to emphasize overall calorie reductions and minimization of carbohydrate [16]. especially added sugars and refined grains, in favor of the consumption of nonstarchy vegetables and foods that are high in protein [35].

However, emerging data demonstrates that there are marked interindividual responses to food [17], attributed to differences in physical activity [36], gut microbiome [18,19,37], and genetics [38], including in variations in skeletal glucose transporters related to insulin resistance [39]. For example, a study conducted in the United States among nondiabetic individuals with a mean BMI of 27 found PPGR to a standardized meal of bagel and cream cheese ranged from 6 to 94 mg/dL·h [20]. A similar study conducted in Israel enrolled nondiabetic individuals of whom 3-quarters had a BMI ≥ 25 and found mean PPGR to bread and butter of 44 mg/dL·h but the bottom decile had responses of ≤ 15 mg/dL·h and the top decile has responses ≥ 79 mg/dL·h [18]. Similar data have been generated for individual without diabetes in the United Kingdom and the United States [19,20], and for individuals with type 1 diabetes in Israel [40].

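### The only stated summary of interindividual PPGR variability is the range of observed test-meal responses, which does not separate differences between people from variation within a person

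*Protocol article*

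**What the plan says.** The Objective is to "characterize the PPGR variability among individuals with diabetes living in India". The Discussion (Study Implications) states the matching hypothesis: "We hypothesize that there will be substantial interindividual variability in PPGR".

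For this aim the Statistical Analysis Plan names one summary: "Descriptive statistics will be used to plot the range of PPGRs responses to standardized test meals". The same sentence adds a correlation between PPGR and the nutrient content of logged meals. The plan also deletes meals with PPGR below 5 mg/dL·h after at least 40 g of carbohydrate.

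Table 1 (Follow-Up Procedures) schedules seven standardized breakfasts:
- Days 3 to 6: four supplemented versions, once each, for example "Fiber supplement with standardized test meal".
- Day 10: the unmodified meal, once.
- Days 11 and 12: "Standardized test meal with postmeal exercise", listed on both days.

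The article states no use of the Day 11/12 pair as a replicate. The only other repeats are contingent: "If a test meal was not consumed as intended, participants are provided with the option to repeat the meal". Under Table 2 the same section tells participants that, in the hours before and after the standardized breakfast, they should fast and "during these fasting periods, limit exercise".

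**The concern.** The spread of observed responses across people is the sum of two things: how far people's usual responses differ, and how far one person's response varies from one occasion to the next. The second part includes day-to-day physiology, differences in home preparation and sensor error. The planned plot shows only the sum. Some range would appear even if everyone had the same average response, and a minimum-to-maximum range also widens as more people are enrolled. The single noise-reduction step described, a median baseline over the 30 minutes before the meal, does not remove occasion-to-occasion variation in the response.

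The argument for personalized diets needs differences between people that persist. A wide plotted range could be read as showing them when it does not.

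The nutrient correlation has a similar weakness if it is computed across all logged meals. It would then mix the effect of one person eating more carbohydrate with differences between people who habitually eat more or less of it.

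**Working it through.** **Inputs.** The document gives no within-person or between-person variance and no ICC, so there is no stated figure of that kind to reproduce. The sample size is consistent: 1050 × 0.95 = 997.5, or about 1000 evaluable people. The most usable spread figures are those cited from a study of nondiabetic people (Study Implications): bottom decile at or below 15 mg/dL·h, top decile at or above 79 mg/dL·h, mean 44. The ICC is assumed, from 0.3 to 0.9.

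**Step 1: spread of one response per person.** With between-person variance B and within-person variance W, the observed variance is B + W and ICC = B/(B + W). Observed SD divided by between-person SD is therefore 1/√ICC.

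**Step 2: on the cited scale.** The observed 10th-to-90th percentile spread is 79 − 15 = 64 mg/dL·h. Under normality the SD is 64/(2 × 1.2816) = 24.97. The between-person part of the 64 is 64 × √ICC.

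**Step 3: the low-PPGR deletion.** Table 2 gives the test meals 61.5 to 64.1 g of carbohydrate, so the rule applies to all of them. Responses for 1000 people were simulated with total SD 24.97, and those below 5 mg/dL·h were removed. A normal model with mean 47 lost about 4.6% of responses. A lognormal model with mean 44 (ICC on the log scale) lost almost none.

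| Assumed ICC | SD ratio, no deletion | Between-person part of 64 | SD ratio after deletion, normal | Range ratio after deletion, normal | Range ratio after deletion, lognormal |
|---|---|---|---|---|---|
| 0.3 | 1.83 | 35 | 1.65 | 1.38 | 206.4/92.5 = 2.23 |
| 0.5 | 1.41 | 45 | 1.28 | 1.07 | 208.9/126.8 = 1.65 |
| 0.7 | 1.20 | 54 | 1.08 | 0.91 | 208.4/161.0 = 1.29 |
| 0.9 | 1.05 | 61 | 0.96 | 0.80 | 209.3/189.5 = 1.10 |

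Each ratio compares the observed spread with the true between-person spread; a value above 1 is an overstatement. Under the normal model the minimum-to-maximum range falls below the true range from an ICC of about 0.6 upward (0.98 at 0.6). Under the lognormal model it stays above it throughout.

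**Step 4: what the existing replicate could deliver.** For n pairs, SE(ICC) is approximately (1 − ICC²)/√n. With 1000 complete Day 11/12 pairs:
- ICC 0.3: 0.91/31.6 = 0.029
- ICC 0.5: 0.75/31.6 = 0.024
- ICC 0.7: 0.51/31.6 = 0.016

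If the meal filters left only 500 pairs, the range would be 0.023 to 0.041.

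**The case against.** The strongest reply is that this is one sentence in a condensed article. A full analysis plan may hold a variance model, and plotting a range does not exclude one. That stands as far as it goes: one can say only that no use of the Day 11/12 pair is stated, not that it will go unused. It does not remove the point, because the article names a specific summary for its main aim, and that summary, followed as written, does not measure the stated quantity.

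Several stronger readings are tempting and are not supported:
- *The plot will use single responses.* The article does not say so. It fits the five once-only meals, but seven test breakfasts are scheduled and the handling of the repeated one is not described.
- *The range must overstate.* The direction depends on the ICC, on the shape of the distribution and on the low-PPGR deletion, as the table shows.
- *The hypothesis cannot fail.* Its second part, that models will predict individual PPGR accurately, is tested in held-out participants and can fail. That test does not supply the missing variance split, since a correlation over aggregated meals can be driven by meal content.
- *The nutrient correlation is pooled over meals.* The article does not say whether it is pooled, per person or clustered.

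The replicate also has limits. Days 11 and 12 are consecutive and a sensor is replaced only when a problem is found, so the pair normally shares one sensor as well as a person's habitual preparation. Stable differences of either kind remain in the between-person part. The pair is also listed with exercise, so its repeatability may not carry over to the unmodified meal.

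**Conclusion.** The point holds in limited form. The only stated summary of interindividual variability confounds between-person with within-person variation and cannot by itself support a claim about stable differences between people. It will usually overstate the between-person spread, by 5% to 83% on the SD scale for assumed ICCs of 0.9 down to 0.3, before the low-PPGR deletion. With the deletion the excess can shrink or reverse at high ICC if responses are roughly normal. The true size cannot be computed from the document, because it gives no ICC and its spread figures come from nondiabetic people. The definition of PPGR and the sample size are unaffected. The change is worth making because the data that would resolve the question are already scheduled.

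**What to change.** Keep the raw range and add a linear mixed model for the seven standardized breakfasts, with meal condition fixed, participant random and a participant-by-condition random term. That last term matters: with a random intercept alone, a person's particular response to a particular meal version would be counted as within-person noise. Only the Day 11/12 pair separates it from residual variation, which requires assuming a common residual variance across conditions.

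Report between-person SD, within-person SD and ICC with intervals. State that the pair normally shares one sensor and a person's habitual preparation, so stable differences in either stay in the between-person part. State also that a standard error of 0.016 to 0.029 for the ICC is a best case requiring 1000 complete pairs.

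If the nutrient correlation is computed across all logged meals, centre nutrients on each person's mean and report within-person and between-person associations separately.

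Separately, reconcile Table 1's postmeal exercise on Days 11 and 12 with the instruction to limit exercise after the standardized breakfast, because the meaning of the replicate depends on which condition applied.

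The cost is analysis wording, a little more analysis and probably a smaller reported between-person spread. No new data are needed.

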### Sample Size Considerations

A total of 1050 individuals will be targeted for recruitment. Assuming a 5% loss to follow-up, this corresponds to 1000 evaluable individuals at the end of the study. The study has been designed to predict postprandial glucose responses based on individual characteristics and 1000 participants followed for 14-days will result more than 4 million glucose readings (assuming glucose readings from the CGMs every 5 minutes) and 42,000 meals (assuming 3 meals per participant per day). This volume of data will also provide more than 80% power to detect correlations of a magnitude of *r*=0.13 (*R*^2^=0.02) with *P*<.005. We will also be sufficiently powered to detect effects of *r*=0.17 (*R*^2^=0.03, ie, explaining 2.7% of interindividual variation) with *P*<.001, that is, accounting for 5000 independent hypothesis tests.

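### Power for correlations is credited to the volume of meals and readings but fits about 1000 participants, while the planned PPGR-composition correlation is on repeated meals with no stated unit of analysis

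*Protocol article*

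**What the plan says.** Protocol article, Statistical Analysis Plan: under descriptive statistics, the plan will show the range of PPGR to the standardized meals and "the correlation between PPGR and the nutritional composition of the logged meals (ie, carbohydrates, fat, and protein"). Outside the prediction model, this is the only correlation named between PPGR and a candidate factor. No test, P value, interval or treatment of repeated meals is attached to it.

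Protocol article, Sample Size Considerations: the recruitment target is 1050, reduced for dropout as follows: "Assuming a 5% loss to follow-up, this corresponds to 1000 evaluable individuals at the end of the study". Next, the section counts more than 4 million glucose readings and "42,000 meals (assuming 3 meals per participant per day"). For r=0.13 at P<.005 it then states: "This volume of data will also provide more than 80% power to detect correlations of a magnitude of" that size. It also claims sufficient power for r=0.17 at P<.001. It describes the r=0.17 effect as a share of interindividual variation and says that this level accounts for 5000 independent tests. The unit of analysis is not named.

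Protocol article, Abstract, Objective: the study aims to characterize PPGR variability and "to identify factors associated with these differences".

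Protocol article, Follow-Up Procedures: "Participants are followed for 14 days". Table 1 ("Meal schedule during the at-home study period") lists three meal slots a day, and the day 1 breakfast slot is fasting.

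**The concern.** The sample-size text moves from counts of readings and meals straight to power for correlations, as if the volume of repeated measurements produced that power. The only such correlation the plan names is measured on meals. Meals from one person are not independent: they share that person's general PPGR level, which the study expects to differ substantially between people, and to some degree that person's habitual diet.

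Two things follow. First, one coefficient over all meals combines two different relations: how a person's response changes from meal to meal with composition, and how people who habitually eat differently differ in PPGR. The first is what personalized dietary advice needs, and the pooled value may be smaller or larger than it. This holds even if the correlation is purely descriptive. Second, if the stated P thresholds or confidence limits were applied to pooled meals as though they were independent, they would be too optimistic.

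**Working it through.** **Inputs from the Protocol article.** N = 1000 evaluable (1050 × 0.95 = 997.5); r = 0.13 at P<.005; r = 0.17 at P<.001; 5000 tests; 14 × 3 = 42 meals per person. Table 1 leaves 41 eaten meals, because day 1 breakfast is fasting. Filtering removes some meals and logged snacks add some. **Assumptions:** two-sided tests, and all ICCs and within- and between-person correlations used below. The article gives none of these.

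**1. Reproducing the stated power.** Fisher z: power = Φ(atanh(r)·√(N−3) − z₁₋α/₂).
- r=0.13, α=.005, N=1000: 0.1307 × 31.58 − 2.807 = 1.321, so 90.7%.
- r=0.17, α=.001, N=1000: 0.1717 × 31.58 − 3.291 = 2.130, so 98.3%.
- r=0.17, α=0.05/5000=0.00001, N=1000: 5.420 − 4.417 = 1.003, so 84.2%.

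The claim of more than 80% is true with participants as the unit.

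**2. Could the figures come from meals?** N for 80% power = ((z₁₋α/₂ + 0.842)/atanh(r))² + 3. This gives 782 for r=0.13 at .005 and about 582 for r=0.17 at .001. Inverting the formula gives the smallest r detectable with 80% power:

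| N | α=.005 | α=.001 | α=.00001 |
|---|---|---|---|
| 1000 | 0.115 | 0.130 | 0.165 (R²=2.7%) |
| 42,000 | 0.018 | 0.020 | 0.026 |

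The printed r values and the 2.7% are on the scale of the N=1000 row. With 42,000 independent meals the detectable r would be about 0.02. The figures are person-level.

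**3. Mixing in a single coefficient.** Pooled r = √(ICCx·ICCy)·r_between + √((1−ICCx)(1−ICCy))·r_within. Assume ICC 0.3 for PPGR, ICC 0.2 for the nutrient and r_within = 0.40. The within part is √0.56 × 0.40 = 0.299, and the weight on the between part is √0.06 = 0.245.
- r_between = −0.3: 0.299 − 0.073 = 0.23
- r_between = 0: 0.30
- r_between = +0.3: 0.299 + 0.073 = 0.37

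Simulation gave 0.227, 0.301 and 0.373. With both ICCs at 0.3 and r_between = −0.3, the pooled value is 0.7 × 0.40 − 0.3 × 0.3 = 0.19.

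**4. If P values were attached with meals treated as independent.** Design effect DE = 1 + 40·ICCx·ICCy for 41 meals each. The actual false-positive rate at nominal .005 is 2·(1 − Φ(2.807/√DE)).

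| ICC PPGR | ICC nutrient | DE | Formula | Simulated |
|---|---|---|---|---|
| 0.3 | 0 | 1.0 | 0.5% | 0.3% |
| 0.05 | 0.05 | 1.1 | 0.7% | not run |
| 0.05 | 0.2 | 1.4 | 1.8% | not run |
| 0.3 | 0.1 | 2.2 | 5.8% | 5.0% |
| 0.3 | 0.2 | 3.4 | 12.8% | 13.8% |
| 0.3 | 0.3 | 4.6 | 19.1% | 19.3% |

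Simulated rates use 600 runs of 1000 people × 41 meals. Correct standard errors are √DE times the naive ones: about 1.05 times at DE 1.1 and 2.1 times at DE 4.6. Even at the extreme (both ICCs equal to 1, DE = 41), the effective sample is 41,000/41 = 1000, so clustering does not take it below the number of participants.

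**The case against.** The correlation is presented as description, with no P value or interval, and the article never says that meals are pooled as independent. It condenses a fuller plan that is not shown, and handling of repeats may be settled there. The person-level power figures and the reference to interindividual variation suggest that person-level tests were intended. The prediction model already respects the participant: cross-validation divides participants into groups, and performance is judged on meals from held-out participants. Common test meals and scheduled meal modifications add within-person variation in composition, which lowers the nutrient ICC and so the inflation.

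Most of this stands, and it rules out three stronger readings that a reader might draw:
- That the plan's own P values are too optimistic. None is attached to this correlation, so the problem is conditional on naive testing.
- That factors such as age, HbA1c or medication will be falsely declared at high rates. The article uses these only as features of the prediction model and plans no pooled meal-level test of them.
- That the study is underpowered or its power overstated. It is not.

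The objection does not remove the rest. The sample-size text itself credits the power to data volume, which is wrong as stated. It also sets P thresholds for correlations, so some formal testing is foreseen. If that testing is not the meal-level correlation, the article names no correlation to which the power applies. Mixing needs no P value to matter.

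**Conclusion.** The point holds in a limited form. The power statement is numerically sound for 1000 participants but is attributed to meals and readings, and its unit is unnamed. The one PPGR-composition correlation in the plan is on meals. Reported as a single coefficient, it would blend two relations; in the illustrations a within-person r of 0.40 becomes anything from 0.19 to 0.37. Inference that ignored the participant would have a false-positive rate for nutrients of roughly 0.7% to 19% against a nominal 0.5%, for assumed ICCs of 0.05 to 0.3, and no inflation if composition does not cluster by person. All of these sizes rest on assumed ICCs and correlations. The misattribution of power and the difference in units rest on the article's own figures and wording.

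**What to change.** **Statistical Analysis Plan.** Estimate the PPGR-composition association with a linear mixed model of meal-level PPGR that has a participant random intercept. Split each nutrient into the participant's mean and the meal's deviation from it, and report within-person and between-person associations separately. A within-person (repeated-measures) correlation is a simpler alternative for the first of these. Base any interval or P value on the participant as the independent unit.

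**Sample Size Considerations.** State that the power refers to 1000 participants, not to meals or readings: about 91% for r=0.13 at P<.005 and, for r=0.17, about 98% at P<.001. Do not describe P<.001 as covering 5000 tests. On a Bonferroni basis at 5% overall it covers 0.05/0.001 = 50; 5000 tests require 0.00001, where power for r=0.17 is about 84%.

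**Cost.** Changes of wording and of analysis method only, on data already being collected, with no extra participants. The downside is wider intervals and fewer nominally significant associations.
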